#### Objective 3: Evaluate the accuracy of proposed wireless technology as compared to standard monitoring technology in the NICU

To evaluate the accuracy of the ANNE^®^ we will compare the data obtained by the wireless system to the standard of care. The number of data points acquired for comparison during each hour of participation in either phase 1 or 2 is shown in Table 5. Total number of data points acquired per hour and throughout the entire study are provided in Tables S2 and S3. To comprehensively describe how ANNE^®^ compares to the Phillips monitor, several signal processing and statistical methods have been selected following an extensive literature review. These techniques have been separated into four classes, according to their overall objective: (1) methods that describe signal quality (2) methods that describe the continuity of the data, (3) methods that compare the raw signals from ANNE^®^ and Phillips directly, and (4) methods that compare summary statistics derived from these signals. A list of the statistical methods that will be utilized are outlined in Table 6.

**Table 5 table-5:** Expected number of data points obtained per participant per hour.

	Philips intellivue MX450	Wireless ANNE^™^ monitoring system
ECG	1.8 × 10^6^	9.207161125 × 10^5^
PPG	4.5 × 10^5^	2.303262956 × 10^5^
Resp signal	2.25 × 10^5^	1.152 × 10^5^
HR	3.515625 × 10^3^	3.6 × 10^3^
SpO_2_	3.515625 × 10^3^	3.6 × 10^3^
RR	3.515625 × 10^3^	3.6 × 10^3^
Temperature (axial & chest respectively)*	1	9 × 10^2^
Skin temp. limb	N/A	9 × 10^2^
3-axis Accel.	N/A	1.5 × 10^6^
Total	2.485547875 × 10^6^	2.778842408 × 10^6^

**Note:**

* Temperature is recorded manually by nurse every hour.

**Table 6 table-6:** Analytical methods to be implemented.

Measure	Applicable methods
Signal quality	Time-warped polynomial filtering (TWPF) Signal averaging Probability distribution function (PDF) Power spectrum
Continuity of the signal	FIR antialiasing lowpass filtering Movement artifact removal Data segmentation
Direct comparison of the raw signals	Cross-correlation function Probability distribution function (PDF) Power spectrum Impulse response function (IRF) Box-jenkins system identification Bland-altman method Lin’s concordance correlation coefficient (CCC) Intraclass correlation coefficient (ICC) Paired *t*-test Equivalence testing
Comparison of derived statistics/signals	Lin’s concordance correlation coefficient (CCC) Intraclass correlation coefficient (ICC) Paired *t*-test Equivalence testing ANOVA *F*-test

Table 5 Expected number of data points obtained per participant per hour.

Quality of the signals—by quantifying the noise level of each device. This will be accomplished *via* signal averaging and time-warped polynomial filtering (TWPF). Both methods attempt to clean a noisy signal such as an ECG and produce a deterministic product. By removing this deterministic component from the raw signal, a noise signal may be obtained for each device. Statistical parameters including variability metrics and the signal-to-noise ratio (SNR) will be used to describe the overall quality of each device for measuring vital signals. These parameters will be accompanied by appropriate probability density functions (PDF) and power spectra.

Continuity of the signals—pre-processing will be used to divide the data into segments of connection loss, corruption due to significant movement artifact, and usable portions of signal recordings. From here, a set of statistics can be used to describe the technical reliability of ANNE^®^, including the number and duration of interruptions, the average period between consecutive interruptions, as well as the portion of data deemed unreliable due to increased movement. Small segments of interruption (<2 s) will be interpolated to yield longer segments of continuous monitoring. Performing this analysis on the data acquired from both phases will further allow us to study how increasing recording length potentially exacerbates these statistics.

Compare the raw signals from ANNE^®^ and Phillips directly—a preliminary step requires that the signals from ANNE^®^ be resampled to produce segments with an equal number of data points as the Philips monitor (this will be completed as part of the pre-processing in the second class of analysis). Any recording period with under 2 h of usable paired data from the ANNE^®^ and the Phillips will be excluded from comparative analysis. Once equal data samples have been obtained from all usable recordings, the cross-correlation will be used to quantify the latency between matching signals. Performing this operation on segmented epochs throughout a recording will also allow us to determine whether the delay varies with monitoring time or remains constant. The length of epoch segments will be determined based on preliminary analysis. In the time domain, the (PDF) will be used to compare the amplitude structures of signals, while system identification *via* linear models will be used to study the relationship between ANNE^®^ and the Philips monitor. In the frequency domain, the power spectrum will be derived to compare the frequency contents of each signal and extract statistics for the third class of techniques. Lastly, statistical methods, such as the Bland-Altman method, paired *t*-tests, and correlation coefficients, will be implemented to evaluate the agreement between paired measurements or samples.

Compare summary statistics—from the raw signals, summary statistics will be derived and compared to further validate the reliability of ANNE^®^. A detailed list of statistics, both in the time domain and frequency domain, for the various vital signals are outlined in Table 3 alongside traditional measures such as the average heart rate over a specified period, the average respiratory rate over a specified period, and the number of heart beats or breaths detected and/or missed by each device. Graphical representations of desired statistics used for analysis are shown in Fig. 5. The same statistical procedures previously mentioned will be applied once more, this time comparing paired statistics as opposed to matching sample points.

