**Note:**

SDNN, SD of normal- to- normal (NN) or R-wave- to- R-wave intervals; SDANN, SD of the averages of NN intervals in all 5 min segments of the entire recording; SDNNi, mean of the SDs of all NN intervals; RMSSD, root mean square of the differences between adjacent NN intervals; (f) SDSD, SD of differences between adjacent NN intervals; TINN, baseline width of the minimum square difference triangular interpolation of the highest peak of the histogram of all NN intervals measured.

The quality of the signal will be assessed by quantifying the average noise level for each signal, for both monitoring devices.

Continuity of signal will be assessed by quantifying the frequency and duration of connection loss, corruption of signal due movement artifacts, as well as quantification of portion of usable data from each recording period.

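### ANNE waveforms are up-sampled about 1.95-fold to match Philips, and noise and SNR are compared at unequal sampling rates with no common frequency band

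*Protocol article*

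**What the plan says.** Objective 3 divides its methods into four classes: signal quality, continuity, direct comparison of raw signals, and comparison of summary statistics.

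- **Direct comparison.** The ANNE signals are to "be resampled to produce segments with an equal number of data points as the Philips monitor". This is assigned to the pre-processing of the continuity class. Amplitude distributions, power spectra, linear system identification, Bland-Altman analysis, paired t-tests and correlation coefficients follow. Table 6 adds impulse response functions, Box-Jenkins identification and equivalence testing.
- **Sampling.** Table 5 ("Expected number of data points obtained per participant per hour") gives ANNE counts of "9.207161125 × 10^5" for ECG and "2.303262956 × 10^5" for PPG. The Philips counts are 1.8 million and 450,000. The respiratory signal has 225,000 points on Philips and 115,200 on ANNE.
- **Noise.** The outcome section plans "quantifying the average noise level for each signal, for both monitoring devices". The method is to estimate a clean signal and subtract it: "By removing this deterministic component from the raw signal, a noise signal may be obtained for each device". Then "the signal-to-noise ratio (SNR) will be used to describe the overall quality of each device". Spectra and distributions are to accompany these figures.
- **Filtering.** The only low-pass filter in Table 6 is listed under continuity, without a cutoff. The article names neither a resampling method nor a common frequency band for the noise comparison.

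**The concern.** Two separate issues arise because the Philips waveforms are sampled about twice as fast as the ANNE waveforms.

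First, matching ANNE to the Philips point count raises the slower signal to the faster rate. No resampling can add information above ANNE's Nyquist limit, yet the planned spectra and fitted linear models would span the Philips range. In the upper half of that range, a difference between the spectra says nothing about how well ANNE measures. The fitted input-output relation there is poorly determined and partly reflects the resampling filter. Point-by-point methods would also see nearly twice as many pairs as ANNE has samples.

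Second, noise power depends on the bandwidth over which it is collected. If each device's noise is taken from its own raw signal at its own rate, two sensors of equal quality can receive different SNRs. Since SNR is meant to describe device quality, a reader could take a sampling-rate difference for a quality difference.

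**Working it through.** **1. Table 5 totals reproduce.**
- Philips: 1,800,000 + 450,000 + 225,000 + 3 × 3,515.625 + 1 = 2,485,547.875.
- ANNE: 920,716.1125 + 230,326.2956 + 115,200 + 3 × 3,600 + 900 + 900 + 1,500,000 = 2,778,842.408.

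Both agree with the table, so the entries can be used as read.

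**2. Rates and up-sampling.** Rate = count / 3,600. Factor = Philips / ANNE. Surplus share of output = 1 − ANNE / Philips. Nyquist limit = rate / 2.

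| Waveform | Philips rate (per s) | ANNE rate (per s) | Factor | Surplus | Nyquist limit, Philips / ANNE (Hz) |
|---|---|---|---|---|---|
| ECG | 500 | 255.75 | 1.955 | 48.8% | 250 / 127.9 |
| PPG | 125 | 63.98 | 1.954 | 48.8% | 62.5 / 32.0 |
| Respiration | 62.5 | 32 | 1.953 | 48.8% | 31.25 / 16 |

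The 48.8% is the share of output points beyond the number of measured ANNE samples. It is not the share of points that are interpolated. Because the factor is not an integer, nearly all output points are computed: for respiration (125/64) only 1 in 125, or 0.8%, falls on an original sample time.

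For heart rate, SpO2 and respiratory rate values, ANNE goes from 3,600 to 3,515.625 per hour. This is a factor of 0.977, a slight down-sampling.

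**3. Effect of the interpolation method.** In a simulation of a signal with flat content from 0 to 100 Hz, taken from 255.75 to 500 per second, band-limited interpolation gave no error beyond machine precision. Linear interpolation gave about 22% relative root-mean-square error and lost about 25% of the variance.

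**4. Counting points.** If points were treated as independent, up-sampling alone would shrink a naive standard error by √1.955 = 1.40.

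**5. SNR.** Assume flat noise of equal density in both devices, the same front-end limit F, and anti-alias filtering of each device at its own Nyquist limit. Noise power is then proportional to min(F, Nyquist limit), and the ECG gap in ANNE's favour is 10·log10 of the ratio of the two bandwidths. The documents give no F, so a range is shown:
- F at or below about 127 Hz: ratio 1.00, gap 0 dB.
- F = 150 Hz: 10·log10(150 / 127.9) = 0.7 dB.
- F = 250 Hz: 10·log10(250 / 127.9) = 2.9 dB.
- Flat noise to 250 Hz and no anti-alias filter on the slower device: noise folds back and the simulated ratio is 1.002, about 0 dB.

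The PPG and respiration maxima are also about 2.9 dB (10·log10 of 1.954 and of 1.953). Restricting both ECGs to a common band at or below 127.9 Hz gives 0 dB throughout under these assumptions.

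**The case against.** The strongest reply is that no bias has been shown. The article gives sample counts, not front-end bandwidths or noise spectra, and the SNR gap may be zero. SNR is descriptive, no pass/fail rule depends on it, and the spectra reported beside it would reveal a bandwidth difference. Band-limited up-sampling does not distort agreement, and an article may leave the interpolation method to a fuller document. All of this stands, and it limits the point to a possible confounder. It does not remove the point: the article itself fixes the direction of resampling, and a visible bandwidth difference still leaves the SNR uncorrected.

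Four stronger readings are tempting, and the documents do not support them.
- A reader might infer that resampling causes the SNR problem. It does not: noise is taken from the raw signal in the first class, whereas resampling belongs to the second.
- A reader might infer that ANNE is certain to look cleaner. That needs noise above ANNE's Nyquist limit that Philips retains, which is not stated. If the two front ends filter differently, the gap could even reverse, but that would not be a sampling-rate effect.
- A reader might infer that the vital-sign accuracy results are compromised. Heart rate, SpO2 and respiratory rate values are not up-sampled, and the frequency-domain ECG metrics in Table 3 lie below 0.4 Hz.
- The uneven ANNE counts in Table 5 match rounded sampling intervals (3,600 / 0.00391 and 3,600 / 0.01563), and a reader might infer clock drift. Nothing says these expected counts serve as a time base. BioDASh synchronises the streams, and latency is checked by epoch with cross-correlation.

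**Conclusion.** The point holds as two limited statements. The plan up-samples the ANNE ECG, PPG and respiratory waveforms about 1.95-fold. This leaves 48.8% of output points surplus to the measured samples, and no measured ANNE content above about 128, 32 and 16 Hz in the spectra and system identification. This follows from Table 5 and the resampling sentence without further assumption. Separately, the SNR comparison has no common band and can differ by 0 to about 2.9 dB between equally good sensors. That range assumes equal flat noise and a shared but unknown front-end limit.

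The consequence is confined to the waveform and signal-quality analyses. It is a worthwhile improvement to the plan, not evidence that its accuracy results would be wrong.

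**What to change.** - In the paragraph on direct comparison, reverse the direction for waveforms: anti-alias filter the Philips ECG, PPG and respiratory signals and down-sample them to the ANNE rate, on a common grid set by the recorded timestamps. Name the resampling method.
- In the paragraph on signal quality, state that noise, SNR and spectra are computed for both devices within the same passband, with its upper edge at or below ANNE's Nyquist limit. Set it lower if either front-end filter proves narrower. Use the same band for system identification.
- State that resampled points are not counted as independent pairs in tests or intervals.

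The cost is a few sentences and a change in the MATLAB pre-processing. No new data are needed, and Table 6 already lists an antialiasing low-pass filter. The one loss is that Philips content above ANNE's Nyquist limit leaves the head-to-head comparison. It can be described separately.

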#### Objective 3. Evaluate the accuracy and coverage of the proposed wireless technology as compared to standard monitoring technology in the NICU

Accuracy will be assessed by comparing both the contents and the quality of the data obtained by the ANNE^®^ sensors and the standard monitoring technology.

In terms of the contents, the recorded data of the raw heart rate (HR), temperature, oxygen saturation (SpO_2_), and respiratory rate (RR) obtained by the ANNE^®^ sensors will be compared to the raw signals obtained by the standard monitoring system. A detailed list of the statistics that will be obtained from the data for comparison can be found in Table 3.

**Table 3 table-3:** List of desired test statistics derived from raw monitor signals.

Heart rate	Average heart rate per epoch (*via* histogram); number of bradycardias and tachycardia per hour; average and maximal duration of bradycardias (<100 beats/min) and tachycardia (>160) per recording (8-h epoch in phase I, 24-h epoch in phase II); number of bradycardias and tachycardia >10 s per hour or per epoch; average heart rate per epoch (*via* tachogram).
ECG (time domain metrics)	minimum, maximum, and median NN interval (*i.e*., the interval between successive R-waves); standard deviation of the NN intervals (SDNN); the standard deviation of the averages of NN intervals in all 5-min segments of the recording (SDANN); the mean of the standard deviations of all NN intervals for all 5-min segments of the recording (SDNNi); the percentage of adjacent NN intervals differing by >50 ms (pNN50); root mean square of successive differences of NN intervals (RMSSD); total number of all NN intervals divided by the height of the 32-bin histogram of all NN intervals (triangular index; HRVTi); and the baseline width of the minimum square difference triangular interpolation of the highest peak of the 32-bin histogram of all NN intervals (TINN).
ECG (frequency domain metrics)	TP: total power (<0.4 Hz), VLF: very low frequency (<0.04 Hz), LF: low frequency (0.04–0.15 Hz), HF: high frequency (>0.15 to <0.4 Hz), and LF/HF ratio using the Welch periodogram
Oxygen saturation	Average, median and interquartile range of SpO_2_ and percentiles (5^th^ and 95^th^); percentage time with values in 5% groupings between 70% and 100%; percentage times spent with SpO_2_ below 80% and above 95%; values in 5% groupings between 70% and 100%

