### Sample size

A convenience sample size of 48 neonates was determined, 24 infants for each phase. However, after data is collected from the first 10 patients, an interim analysis will be performed to determine the precision of measurements between the Phillips and the ANNE^®^ One sensors for each of the parameters. Following that, a reassessment of the appropriate sample size will be performed based on this analysis.

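### The paired t-test is given the task of evaluating agreement between ANNE and Philips, but it tests only whether the mean difference is zero

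*Protocol article*

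**What the plan says.** The relevant text is in the protocol article, Statistical methods, Objective 3.

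- The paragraph on comparing the raw signals ends by saying that methods "such as the Bland-Altman method, paired *t*-tests, and correlation coefficients, will be implemented to evaluate the agreement between paired measurements or samples".
- The next paragraph extends this to the summary statistics of Table 3: "The same statistical procedures previously mentioned will be applied once more, this time comparing paired statistics as opposed to matching sample points".
- In Table 6, the row for direct comparison of raw signals includes Bland-Altman, Lin's CCC, ICC, the paired t-test and equivalence testing. The row for derived statistics has CCC and then "Intraclass correlation coefficient (ICC) Paired *t*-test Equivalence testing ANOVA *F*-test". Bland-Altman is not in that second row.
- The Sample size section states: "A convenience sample size of 48 neonates was determined, 24 infants for each phase". It plans an interim analysis of measurement precision after the first 10 patients, followed by a reassessment of the sample size.

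The article gives no SD of differences, equivalence margin or significance level for these comparisons.

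**The concern.** Agreement between two monitors has two parts: how far apart they are on average, and how widely individual differences scatter around that average. The paired t-test addresses only the first, and takes zero difference as its null hypothesis. Two consequences follow.

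- A small, clinically trivial bias becomes significant once the differences are precise enough, so a close device looks worse because it is consistent.
- Greater scatter inflates the standard error and makes significance less likely, so an erratic device looks better because it is erratic.

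The second is the wrong direction for an accuracy study. The abstract's Methods put accuracy in the primary outcome alongside feasibility and safety, so a sentence in the results that cites a t-test as evidence for or against agreement would bear on a headline conclusion.

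**Working it through.** **Figures in the plan.** There is no power, error rate or margin to reproduce for this comparison. The sample size is consistent with Table 1: 8 subgroups × 6 infants = 48, or 8 × 3 = 24 per phase.

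**Assumptions, not in the document.** The statistic is average heart rate, with one difference (ANNE minus Philips) per infant. Differences are normal and independent, with mean b and SD s in beats/min. The t-test is two-sided at 5%. Equivalence uses two one-sided 5% tests with margin ±5 (±3 as a check).

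**Formulas.**
- Paired t statistic: t = b / (s/√n). Its power comes from the noncentral t distribution with noncentrality b√n/s and n − 1 degrees of freedom.
- Equivalence: both (b + m)/(s/√n) and (m − b)/(s/√n) must exceed the one-sided 5% point of t.
- Limits of agreement: b ± 1.96 s.

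**Close device, b = 1, s = 2.** Limits of agreement are 1 ± 3.92, that is −2.9 to 4.9.
- n = 48: noncentrality 1 × 6.928/2 = 3.46 against a critical value of 2.01. The t-test is significant in 92% of trials.
- n = 24: noncentrality 1 × 4.899/2 = 2.45 against 2.07. It is significant in 65%.
- Equivalence within ±5 passes in essentially 100% at both sizes. With ±3 it passes in at least 99.9%.
- With s = 3, the t-test is significant while equivalence also passes in about 62% of trials at n = 48. At n = 24 this happens in 28% (±3) to 35% (±5).

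**Same bias, growing random error, b = 1.**

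| SD of differences | Limits of agreement | t-test significant, n = 24 | t-test significant, n = 48 |
|---|---|---|---|
| 2 | −2.9 to 4.9 | 65% | 92% |
| 10 | −18.6 to 20.6 | 7.6% | 10.4% |
| 15 | −28.4 to 30.4 | 6.1% | 7.4% |

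As the device gets worse, the test flags it less often. With zero bias, it is non-significant in 95% of trials whatever the SD.

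**Does equivalence of the mean suffice alone?** No. With b = 0, s = 15 and n = 48, equivalence within ±5 passes in about 47% of trials, although the limits of agreement are ±29.4 beats/min. The spread has to be judged as well.

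**The case against.** **The t-test is one of several planned measures.** The same sentence names Bland-Altman first, and Table 6 adds CCC and ICC in both rows. These measures would expose random error. This stands: no information is lost, and the harm is confined to what is concluded from the t-test. Table 6 leaves Bland-Altman out of the derived-statistics row, although the text's repetition of the same procedures may restore it.

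**The article sets no accept/reject rule.** It presents the methods as a comprehensive description, and the Discussion calls the aim exploratory. It never says that a non-significant t-test means agreement. A reader might infer that the t-test and the equivalence test are rival decision criteria with neither ranked. The document does not support that, and ranking and margins may properly sit in an analysis plan that is not shown. What remains is that the article itself gives a difference test the purpose of evaluating agreement.

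**The two tests do not contradict each other.** A significant t-test with a passed equivalence test means a non-zero bias inside the margin. A non-significant t-test with a failed equivalence test is inconclusive. Both readings are coherent, so the figures above show how easily a t-test result can mislead about agreement, not a logical conflict.

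**The erratic-device case depends on the SD.** Averages over hours would remove much random error, and Table 3 defines some statistics per epoch, so an infant may contribute several values. With bias 2, margin ±5 and n = 48, a non-significant t-test with failed equivalence occurs in about 0% of trials at SD 5, 9.5% at SD 10 and 83% at SD 20. This objection limits the size of the effect but not its direction.

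**The F-test has no stated factor.** It appears only in Table 6 and may be meant for groups or phases. A reader might infer that it tests device equality, but the article does not say so.

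**Conclusion.** The point holds in a limited form. The article assigns paired t-tests to the evaluation of agreement, for raw signals and again for derived statistics, and a test of zero mean difference cannot do that job. This is a stated misuse, not a detail left to another document.

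Under the assumed bias of 1 and SD of 2 beats/min, with one independent value per infant, a device that is equivalent within ±5 in essentially every trial would show a significant t-test in about 92% of trials at n = 48 and 65% at n = 24. The percentages depend on the assumed bias, SD and margin. The direction does not: for a fixed non-zero bias, more random error makes the test less likely to flag the device.

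The documents do not support the stronger inference that an erratic device would be accepted as accurate, because Bland-Altman, CCC and ICC are planned and no rule makes the t-test decisive.

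**What to change.** 1. In the raw-signal comparison paragraph and in both comparison rows of Table 6, remove the paired t-test as evidence of agreement. Report the mean difference with its 95% CI as an estimate of bias.
2. Base the accuracy conclusion for HR, SpO2 and RR on two analyses that are already planned: the Bland-Altman limits of agreement and the equivalence test of the bias. Judge both against bounds fixed before the 10-patient interim analysis, so that they are not chosen after precision has been seen. If an analysis plan already holds such bounds, a cross-reference is enough.
3. List Bland-Altman in Table 6 for the derived statistics too, and label CCC and ICC as supportive.
4. Keep the ANOVA F-test only for comparisons between groups or phases, and say so. It should not serve as evidence of device agreement.

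The cost is a change of wording in one paragraph and one table, plus agreement on the bounds. No extra data are needed. The sponsor gives up the option of citing a non-significant t-test as evidence of agreement.

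### Sample-level agreement for SpO2 and heart rate is not conditioned on the level of the vital sign, so it mainly reflects time in the normal range and may not describe error in desaturation or bradycardia

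*Protocol article*

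**What the plan says.** Statistical methods, Objective 3, describes two comparisons of the wireless sensors with the bedside monitor that bear on this point.

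- **Matched samples.** After resampling, Bland-Altman, paired t-tests and correlation coefficients "will be implemented to evaluate the agreement between paired measurements or samples". Table 6 adds Lin's concordance correlation coefficient (CCC), the intraclass correlation coefficient (ICC) and equivalence testing. The stated restriction on the data concerns quantity: "Any recording period with under 2 h of usable paired data from the ANNE^®^ and the Phillips will be excluded from comparative analysis". No restriction, stratum or weight by level of SpO2 or heart rate is given.
- **Derived statistics.** Table 3 lists, for heart rate, "number of bradycardias and tachycardia per hour; average and maximal duration of bradycardias (<100 beats/min) and tachycardia (>160) per recording". For SpO2 it lists "percentage time with values in 5% groupings between 70% and 100" per cent and "percentage times spent with SpO_2_ below 80% and above 95" per cent. These are also compared between devices: "The same statistical procedures previously mentioned will be applied once more, this time comparing paired statistics as opposed to matching sample points".

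Table 6 does not list Bland-Altman for derived statistics, although the text says that the same procedures apply. It is therefore unclear whether the Table 3 quantities get limits of agreement at all.

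Under Sample size: "A convenience sample size of 48 neonates was determined, 24 infants for each phase". Precision between the devices is to be examined after the first 10 patients, and the sample size is then reassessed.

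**The concern.** One bias and one pair of limits describe a device fairly only if its error is about the same over the whole measuring range. If error grows or shifts at low values, and low values fill a small part of the recording, the overall limits come out close to the normal-range limits. The same weighting by time applies to CCC and ICC.

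A monitor is relied on most when saturation or heart rate is low. A reader of the results could take narrow overall limits as evidence of accuracy there, when they say little about it. The interim look is exposed to the same problem: precision pooled over all values could suggest that enough infants have been studied while the low range holds little data.

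**Working it through.** **1. The plan's own figures.** Table 5 gives 3,515.625 heart rate and SpO2 values per infant-hour from the bedside monitor, which is 3,600 / 1.024. The Table 5 totals reproduce as the sums of their rows: 2,485,547.875 for the bedside monitor and about 2,778,842.4 for the wireless system. A complete phase 1 infant (8 h x 4 days = 32 h) yields 32 x 3,515.625 = 112,500 values, and a phase 2 infant (96 h) yields 337,500. For 24 infants in each phase the total is 24 x (112,500 + 337,500) = 10.8 million. Each value counts once, so time at a given level is the weight of that level.

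**2. Overall limits as a mixture.** With time shares p, biases b and SDs s over bands k:

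- m = sum of p_k b_k
- V = sum of p_k [s_k^2 + (b_k - m)^2]
- limits = m +/- 1.96 x sqrt(V)

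*SpO2; all inputs assumed.*

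| Band | Share of time | Bias | SD |
|---|---|---|---|
| below 80% | 0.03 | +4 | 6 |
| 80 to 90% | 0.10 | +1 | 3 |
| above 90% | 0.87 | 0 | 1.5 |

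- m = 0.03 x 4 + 0.10 x 1 + 0 = 0.22
- V = 0.03 x (36 + 3.78^2) + 0.10 x (9 + 0.78^2) + 0.87 x (2.25 + 0.22^2) = 1.509 + 0.961 + 2.000 = 4.469, so SD = 2.114
- overall limits: 0.22 +/- 4.14 = **-3.9 to +4.4**
- limits below 80%: 4 +/- 1.96 x 6 = **-7.8 to +15.8**

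*Range.* Nine settings were run: 1, 3 or 5% of time below 80%, crossed with low-band bias/SD of +2/4, +4/6 or +5/8. The 80 to 90% band stayed at 10%. The widest overall limits are -4.9 to +5.6. The low-band limits run from -5.8 to +9.8 up to -10.7 to +20.7.

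*Heart rate; all inputs assumed.* Error is 0 +/- 3 normally and +15 +/- 12 below 100 beats/min, with 2% of time in bradycardia.

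- m = 0.02 x 15 = 0.30
- V = 0.02 x (144 + 14.7^2) + 0.98 x (9 + 0.3^2) = 7.20 + 8.91 = 16.11, so SD = 4.01
- overall limits: **-7.6 to +8.2** (at 0.5% of time: -6.4 to +6.5)
- limits in bradycardia: 15 +/- 23.5 = **-8.5 to +38.5**
- between 0.5% and 2% of time, 75 to 80% of bradycardia pairs lie outside the overall limits

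**3. Would the Table 3 totals show it?** Matched pairs were simulated and time below 80% was compared between devices.

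*Systematic error, few values just above 80%* (2% of time low, reference 70 to 80% when low, otherwise centred on 94%):

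| Error when low | Reference below 80% | Wireless below 80% |
|---|---|---|
| +5 +/- 4 | 2.01% | 1.01% |
| +3 +/- 3 | 1.99% | 1.33% |
| 0 +/- 6 | 1.99% | 1.54% |

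The total exposes the biased cases clearly. In the unbiased case, 23% of low reference samples are missed.

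*The three-band setting of step 2* (values uniform over 65 to 80, 80 to 90 and 90 to 100%):

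| Low-band bias | Reference below 80% | Wireless below 80% | Low samples missed | Low wireless readings false |
|---|---|---|---|---|
| +4 | 3.0% | 2.8% | 32% | 27% |
| +2 | 3.0% | 3.1% | 23% | 25% |

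Check of the first row: 3.0% x (1 - 0.32) = 2.04% of time is low on both devices, and 2.04% / (1 - 0.27) = 2.8%. Here the totals nearly agree because readings from the 80 to 90% band fall falsely below 80% and replace the missed ones. The overall limits in the first row are -3.9 to +4.2 with readings capped at 100%, so neither planned summary would draw attention to the error.

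**The case against.** The strongest reply is that the plan does look at the low range. Table 3 is introduced as a list for comparison, and the text applies the agreement procedures to those paired statistics. A reader might infer that the SpO2 bands and heart rate cut-offs only describe each device and never enter an agreement analysis. The documents do not support that, and step 3 shows that a systematic shift at low values can be plain in the totals. The plan also compares amplitude distributions and counts detected and missed beats and breaths. This stands: it is a real safeguard, but a partial one. Totals and distributions do not pair readings in time, so they give neither the size of the error at low values nor sample-by-sample concordance.

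Second, nothing says that one pooled set of limits will be reported. That is inferred from the absence of any conditioning. A Bland-Altman plot sets the difference against the mean and can display range-dependent error, and banding could be set out in an analysis plan that is not shown. This also stands, and it limits the point to a recommended addition. The article does, however, fix detail of similar grain, such as the 2 h exclusion, the interpolation of gaps under 2 s and the cut-points themselves.

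Third, a reader might infer that most SpO2 samples sit near the ceiling because many infants breathe room air. Table 1 defines only subgroups A and C that way, 12 of 48, while subgroups D to H, 30 of 48, are on respiratory support. No SpO2 distribution is given. The argument does not need a ceiling effect, only that low values take up a small share of time.

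Last, the error sizes are invented, and a mixture dominated by one component will always resemble it. That is fair: the figures show what the planned summaries could fail to show, not how this device performs.

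**Conclusion.** The point holds in a limited form. The matched-sample analysis of SpO2 and heart rate is not conditioned on level, so overall limits, CCC and ICC will mainly reflect normal-range time and may not describe error in desaturation or bradycardia. The documents do not support the stronger statement that the plan hides low-range error, because the Table 3 comparison can reveal systematic error there. What remains uncovered is the size of the error at low values and whether the two devices read low at the same moments.

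On the assumed inputs, overall SpO2 limits stay within -4.9 to +5.6 points while low-band limits reach -10.7 to +20.7. Time below 80% can agree to within 0.2 percentage points with roughly a quarter to a third of low samples missed. These sizes rest on assumed time shares, biases, SDs and within-band distributions. The conclusion needs only that low values are a small share of time and that error may differ there. The convenience sample of 48 is not called into question. This is an improvement the plan should make, not a fault that invalidates it.

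**What to change.** In Statistical methods, Objective 3, where the raw signals are compared directly, keep the overall figures and add one of the following for matched samples:

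- bias and limits of agreement for SpO2 within the 5% bands of Table 3 plus a band below 70%, and for heart rate within <100, 100 to 160 and >160 beats/min; or
- bias and SD modelled as functions of the mean of the two devices.

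Form the bands on the mean of the two devices, so that neither device's own error decides which band a pair enters. Give intervals clustered by infant, and state the hours and the number of infants in each band. Report the low-band results beside the overall accuracy figure, labelled descriptive. Make the choice before the look at the first 10 patients, so that precision is seen by band there too.

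The cost is a few table rows and no new data. The downside is that the low bands will hold few hours from few infants, so their intervals will be wide and cannot carry a firm accuracy claim.
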